## Abstract

SGLT-2 inhibitor, traditionally used for glycemic control, has several beneficial effects that can help manage heart failure (HF). SGLT-2 inhibitors reduce the risk of cardiovascular mortality in patients with HF. As atrial fibrillation (AF) is closely associated with HF and diabetes mellitus (DM) is a risk factor for AF, we assume that SGLT-2 inhibitors will also show therapeutic benefits regarding AF, especially for rhythm control. This trial has a multicenter, prospective, open, blinded endpoint design. It is a 1:1 randomized and controlled study. A total of 716 patients who are newly diagnosed of AF and DM within 1 year will be enrolled from 7 tertiary medical centers. The trial is designed to compare the effects of SGLT-2 inhibitors and other oral hypoglycemic agents on atrial rhythm control in patients with AF and DM. The primary outcome is the recurrence of AF within a year (including post-antiarrhythmic drugs (AAD) or ablation). The secondary outcomes are the ablation rate within a year, change in AF burden, size of the left atrium, NT-proBNP, the AF symptom score, and the quality of life. This trial will prospectively evaluate the effect and safety of SGLT-2 inhibitors on AF rhythm control in patients with DM. It will provide an invaluable dataset on rhythm control in AF with DM for future studies and offer novel information to assist in clinical decisions. (BEYOND trial, ClinicalTrials.gov number: NCT05029115. https://clinicaltrials.gov/ct2/show/NCT05029115).

## Introduction

Atrial fibrillation (AF) is a common cause of cardiac arrhythmia, and its prevalence increases with age [1,2]. In the United States alone, the prevalence of AF is expected to increase to 12.1 million in 2030 from 5.2 million in 2010 [3]. In addition, owing to the growth in the global prevalence of diabetes mellitus (DM) [4], it has become necessary to manage both AF and DM simultaneously. The Action in Diabetes and Vascular Disease: preterAx and diamicroN-MR Controlled Evaluation (ADVANCE) study showed that AF is relatively common in DM and is associated with a considerably increased risk of cardiovascular events and death in patients with DM [5]. According to the Outcomes Registry for Better Informed Treatment of Atrial Fibrillation (ORBIT-AF) registry, DM is not only a risk factor for AF, but also associated with worse AF symptoms and a lower quality of life [6].

AF and congestive heart failure (CHF) are commonly encountered disease entities that share common risk factors such as hypertension, DM, ischemic heart disease, and valvular heart disease [7,8]. AF and CHF are so intertwined that many questions related to their pathophysiologic relationship are still unknown [9]. It has been suggested that heart failure (HF) increases the risk of AF by elevating atrial filling pressures [10,11], inducing alterations in intracellular calcium [12,13], and disturbing the neuro-endocrinological balance [7]. The Dapagliflozin and Prevention of Adverse Outcomes in Heart Failure (DAPA-HF) trial and The Empagliflozin Outcome Trial in Patients with Chronic Heart Failure and Reduced Ejection Fraction (EMPEROR-Reduced) trial revealed that two sodium–glucose cotransporter 2 (SGLT-2) inhibitors, dapagliflozin and empagliflozin, reduce the risk of cardiovascular death or HF exacerbation, regardless of the presence or absence of DM [14,15]. Besides glucose-lowering, SGLT-2 inhibitors appear to have several other beneficial effects as well.

Recent meta-analyses and retrospective studies have reported that the use of SGLT-2 inhibitors in type 2 DM patients with or without HF, as well as in type 2 DM patients with HF, reduces the incidence rate of AF, atrial flutter, and other cardiovascular events [16–19]. However, few randomized controlled studies have reported the relationship between SGLT-2 and AF, and therefore, reports of detailed prognostic characteristics such as change of AF burden and rhythm control other than the incidence of AF are rare. This trial aimed to determine whether SGLT-2 inhibitors have an advantageous influence on rhythm control of AF and, hence, reduce the adverse outcomes of AF through prospective, randomized, and controlled methods.

## Materials and methods

### Study hypothesis and primary outcome

The primary hypothesis of this study is that the SGLT-2 inhibitor is superior to other oral hypoglycemic medications for rhythm control in patients with AF and DM, diagnosed within the prior year. A step-up treatment will be carried out when the participant’s AF recurs. The recurrence rate of AF will be investigated after performing stepwise rhythm control therapies including anti-arrhythmic drugs (AAD) and ablation. AF is defined as per the 2019 AHA/ACC/HRS Guideline, i.e., irregular R–R intervals (when atrioventricular conduction is present), absence of distinct repeating P waves, and irregular atrial activity [20]. It is checked by 24-h Holter ECG every 3 months and is considered significant when it lasts for > 30 s [21].

### Secondary outcomes

Secondary outcomes are listed in Table 1. AF-free survival will be compared between the two groups as the first of the secondary outcome, analyzed using the Kaplan–Meier method, and documented on curve. AF burden at 3-month follow-up visit, 12-month follow-up visit in those who did not step up and used AAD only for rhythm control, immediately before trying ablation, and at 12-month follow-up visit in those who stepped up and underwent ablation in both the SGLT-2 inhibitor group and the control group will be compared. AF burden is defined as the atrial fibrillation time percentage documented on 24-h Holter ECG [22]. Ablation rate, which is the percentage of patients undergoing ablation, within a year will also be compared between the two groups to identify the efficacy of symptom and rhythm control using SGLT-2 inhibitors. Sinus rhythm is considered stable when either a standard ECG or a 24-h Holter ECG showed no episode of clinically relevant arrhythmia, including AF, at the time of check-up [23]. The proportion of participants with stable sinus rhythm in all participants, regardless of with or without ablation, is compared between the two groups at baseline, 6-, and 12-month follow-up visits.

**Table 1 pone.0280359.t001:** Secondary outcomes.

• Rhythm control • AF-free survival • AF burden at • 3-month F/U visit, 12-month F/U visit in those who did not step up to session 2 • Immediately before trying ablation, 12-month F/U visit in those who stepped up to session 2 • Percentage of patients undergoing ablation within a year • Sinus rhythm maintenance* • Diameter of LA • NT-proBNP • Symptom score (EHRA score) • Quality of life (EQ-5D, SF-12)

*Defined as the absence of clinically relevant arrhythmia (e.g., AF, AFL, sustained VT, and VF).

AF, atrial fibrillation; LA, left atrium; F/U, follow up; NT-proBNP, N-terminal pro-B-type natriuretic peptide; EHRA, European Heart Rhythm Association; EQ-5D, EuroQol-5 Dimension; SF-12, Short Form-12 Health Survey Questionnaire; AFL, atrial flutter; VT, ventricular tachycardia; VF, ventricular fibrillation.

As dilatation of the left atrium (LA) is associated with AF in both pathophysiologic and prognostic perspectives, we will use the LA size as a secondary outcome. Left atrial remodeling induces electrical modification, which is associated with AF. LA structural remodeling is characterized by atrial dilatation [24]. An increase in the LA size at baseline is associated with progressive LA enlargement and AF recurrence. Hence, the LA size can be considered a prognostic factor for spontaneous conversion of AF [25]. As an indicator of LA dilatation, the left atrial diameter (anterior–posterior) will be measured by transthoracic echocardiography (TTE) at baseline and 12-month follow-up visit [26]. N-terminal pro-B-type natriuretic peptide (NT-proBNP) is often elevated in AF and is higher in severe AF [27,28]. As it is a significant secondary outcome, we will measure the level of NT-proBNP in blood and compare their values in the two groups at baseline and 12-month follow-up visit.

The symptom score is compared by using the EHRA score. It is measured at baseline, 3-, 6-, 9-, and 12-month of follow-up visits. The ratio of asymptomatic participants will be compared between the two groups. To compare the quality of life between the two groups, EuroQoL five-dimensional instrument (EQ-5D, www.euroqol.org) and SF-12 (a shortened version of SF-36, www.sf-36.org) Health Survey will be used, and assessments will be conducted between the data on baseline and 12-month follow-up visit.

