### Follow-up and detection of AF recurrence

After their recruitment, the participants will receive baseline and evaluation studies under scrutiny, which include history taking, physical examination, blood sampling, urine sampling, 12-lead ECG, 24-h Holter ECG, TTE, EHRA, EQ-5D, and SF-12. The follow-up schedule will begin with the prescription of oral hypoglycemic agents (Table 5). During each intervention, the following steps were conducted: (1) history taking for the review of AF and DM status, adverse events, and other specific illnesses on every visit; (2) physical examination to evaluate any DM complication, AF, NYHA score, neurologic exam, systolic and diastolic blood pressure; (3) blood sampling for CBC, BUN/Cr, electrolyte, coagulation profile, HbA1c, fasting glucose, AST/ALT, lipid battery, and NT-proBNP; (4) urine sampling for dip stick urinalysis with microscopy and measuring proteinuria (especially for albuminuria); and (5) TTE to measure the LA size and left ventricular ejection fraction (LVEF). Any other additive assessing procedure may be conducted and recorded during the clinical course of the patients.

**Table 5 pone.0280359.t005:** Data-collection requirements.

Investigation	Baseline	3M	6M	9M	12M
Inclusion/Exclusion criteria	X				
Medical History	X	X	X	X	X
Physical Examination	X	X	X	X	X
12-lead ECG	X	X	X	X	X
24-h Holter ECG*	X	X	X	X	X
Blood, Urine sample	X				X
Transthoracic Echocardiography (TTE)	X				X
NT-proBNP	X				X
EHRA Score	X	X	X	X	X
EQ-5D, SF-12	X				X
Adverse Events History**		X	X	X	X

*Patients with an ablation (RFA or 4PVI) will be monitored every 3 months that point on for an additional year.

**To evaluate adverse events, any suitable diagnostic investigation can be performed.

Abbreviations. ECG, electrocardiogram; NT-proBNP, N-terminal pro-B-type natriuretic peptide; EHRA, European Heart Rhythm Association; EQ-5D, EuroQol-5 Dimension; SF-12, Short Form-12 Health Survey Questionnaire.

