Very few studies have quantitatively analyzed the AF burden, represented as the percentage of AF time during the monitoring period, because continuous ambulatory monitoring is needed to calculate the exact AF burden [22]. There are some ongoing clinical trials such as DAPA-AF that attempt to quantitatively evaluate the AF burden using cardiac implantable electronic devices (CIED). On the contrary, we plan to measure the AF burden after randomization of SGLT-2 inhibitors, before and after ablation, by utilizing 24-h Holter ECG, which is an excellent choice in terms of accessibility. Furthermore, our study results and information about the population with AF and DM will provide valuable data for subsequent studies in the future.

The LA size and blood level of NT-proBNP are set as the secondary endpoints, as we speculate that SGLT-2 inhibitors will delay the pathophysiologic course of AF. Remodeling of LA by itself acts as an underlying substrate for AF. In addition, progression of AF further deteriorates the LA function and accelerates LA remodeling, thereby continuing the vicious cycle [46,47]. Degree of abnormality of the LA structure and function can be used to determine the positive association with the electrical burden of AF [47]. Therefore, we plan to evaluate the progress of LA remodeling by measuring the degree of LA enlargement, i.e., change in the LA size by utilizing TTE. In addition, considering that NT-proBNP is often increased in AF and shows positive correlation with the clinical severity of AF [27,28], NT-proBNP can be used for assessing the severity of AF. Finally, the quality of life of all patients will be precisely measured.

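### AF burden is announced as a change, but its comparisons are set only at time points after randomisation; the baseline Holter should be named as a covariate

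*Protocol article*

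**What the plan says.** The Abstract states: "The secondary outcomes are the ablation rate within a year, change in AF burden, size of the left atrium, NT-proBNP", followed by symptom score and quality of life. The Introduction also gives the scarcity of reports on how AF burden changes as part of the rationale.

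The Secondary outcomes section defines the measure: "AF burden is defined as the atrial fibrillation time percentage documented on 24-h Holter ECG". It then sets the comparisons: "AF burden at 3-month follow-up visit, 12-month follow-up visit in those who did not step up and used AAD only for rhythm control", and "immediately before trying ablation, and at 12-month follow-up visit in those who stepped up and underwent ablation". Table 1 gives the same list. The Discussion describes the timing in the same way: "we plan to measure the AF burden after randomization of SGLT-2 inhibitors, before and after ablation".

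A baseline value will exist. Under Follow-up and detection of AF recurrence, the baseline studies are listed as "history taking, physical examination, blood sampling, urine sampling, 12-lead ECG, 24-h Holter ECG, TTE, EHRA, EQ-5D, and SF-12", and Table 5 marks the Holter at baseline.

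The statistical section assigns a chi-square test to recurrence and sinus rhythm. It assigns a t-test on 12-month values to left atrial size, NT-proBNP and quality of life. It assigns nothing to AF burden.

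**The concern.** An outcome called a change needs a starting value, and in a randomised comparison the natural one is the value at randomisation. None of the listed time points supplies it. For its other secondary measures the article does name baseline: sinus rhythm, left atrial diameter, NT-proBNP, EHRA score, EQ-5D and SF-12. AF burden is the exception, so brevity alone is a weak explanation.

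Two things are at stake. First, an analyst following the Abstract and one following the Secondary outcomes section would estimate different quantities. Second, eligible patients run from those with one brief documented episode (Table 3) to those with persistent AF, for whom the rhythm control strategy provides cardioversion. Baseline burden may therefore vary widely between patients, and using it could sharpen the comparison at no cost in data.

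**Working it through.** **Step 1. Is baseline in any listed comparison?**

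| Place | Time points for AF burden |
|---|---|
| Abstract | a change, start not stated |
| Secondary outcomes and Table 1, no step-up | 3 months, 12 months |
| Secondary outcomes and Table 1, step-up | just before ablation, 12 months |
| Discussion | after randomisation, before and after ablation |
| Table 5 | Holter at baseline, 3, 6, 9 and 12 months |

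Baseline is recorded but is not in any listed comparison. A difference from 3 to 12 months, or from before to after ablation, could be formed from the listed visits. Both start after treatment has begun, and the text calls neither a change.

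**Step 2. What could baseline add?** The article states no figure for AF burden, so there is none to reproduce; its sample size of 716 is for the primary outcome. Let ρ be the correlation between baseline and follow-up burden. It is an assumption here, shown over a range. Assume equal variance at both times and set the variance of the follow-up-only comparison to 1. Then:

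- baseline as covariate (linear ANCOVA): 1 − ρ²
- raw change score: 2(1 − ρ)

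| ρ | ANCOVA | Fall in variance | Change score |
|---|---|---|---|
| 0.1 | 0.99 | 1% | 1.8 |
| 0.3 | 0.91 | 9% | 1.4 |
| 0.5 | 0.75 | 25% | 1.0 |
| 0.7 | 0.51 | 49% | 0.6 |

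Since 2(1 − ρ) exceeds 1 whenever ρ is below 0.5, a raw change score is then less precise than ignoring baseline altogether. ANCOVA is never worse than either in this table.

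**Step 3. In terms of power.** Take 358 × 0.9 ≈ 322 per arm, a two-sided 5% level and, purely for illustration, a true difference of 0.2 SD. Power = Φ(0.2 × √(322/2) / √v − 1.960), where v is the relative variance above. With 0.2 × √161 = 2.538:

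- follow-up only: Φ(2.538 − 1.960) = 71.8%
- ANCOVA at ρ = 0.1, 0.3, 0.5, 0.7: 72.3%, 75.8%, 83.4%, 94.4%
- change score at the same ρ: 47.3%, 57.3%, 71.8%, 90.6%

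Equivalently, an effect detectable with 80% power without adjustment would be detected with Φ(2.802/√(1 − ρ²) − 1.960) = 83.6%, 89.9% and 97.5% at ρ = 0.3, 0.5 and 0.7.

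These factors hold for a linear model. For a rank-based or ordinal model they are only a guide.

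**The case against.** The strongest reply is that the article fixes when burden is compared, not how. Covariates for a secondary outcome are commonly left to the analysis plan, which is not shown. That stands as far as it goes. A reader might infer that the plan throws baseline precision away or compares raw follow-up percentages. The article does not say so, because it states no method for AF burden. It does not answer the mismatch, however: an analysis plan would still have to choose between the Abstract and the Secondary outcomes section.

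Other stronger readings also fail:

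- **The change cannot be reported.** It can be computed, because the baseline Holter is collected. It is simply not among the listed comparisons.
- **A chance imbalance in persistent AF would invalidate the result.** An unadjusted comparison of all randomised patients is valid, and its error rate already allows for chance imbalance. Adjustment is a matter of efficiency.
- **The gain is bound to be large.** The correlation may be low. Table 3 requires ECG parameters measured in sinus rhythm, all patients receive an AAD, persistent AF is cardioverted, and one 24-h recording samples paroxysmal AF sparsely.
- **The 3-month comparison plainly covers everyone.** In Table 1 the restriction to those who did not step up can be read as applying to the 3-month visit as well as the 12-month visit.

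**Conclusion.** The point holds as a mismatch between the announced outcome and its definition, together with an opportunity to use a baseline value that the trial already collects. The mismatch is firm and can be seen in the article alone. The gain is conditional: from about 1% of the variance at ρ = 0.1 to 49% at ρ = 0.7, assuming a linear model and equal variances, with ρ undocumented.

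The scope is one secondary outcome. The primary analysis is not affected. Nor does adjustment cure the 12-month and pre-ablation comparisons, which are made in subgroups defined by step-up after randomisation. The 3-month comparison can avoid that selection, because session 1 lasts at least 3 months, but only if it is defined on all randomised patients.

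**What to change.** 1. Make the Abstract and the Secondary outcomes section with Table 1 describe the same outcome, for example AF burden at the stated visits, adjusted for baseline.
2. State that every AF burden comparison includes burden on the randomisation-baseline Holter as a covariate, and do not use a raw change score. Because burden is likely to be skewed with many zeros, use a rank-based ANCOVA or a proportional-odds model on ordered burden.
3. State explicitly that the 3-month comparison includes all randomised patients.
4. Note that the 12-month and pre-ablation comparisons remain subject to selection by step-up, whatever the adjustment.

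The cost is wording only. The Holter is already scheduled in Table 5, and neither the sample size nor the visit schedule changes.

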The rhythm control strategy for AF will be followed, independent of the type of hypoglycemic agents received. This strategy includes two sessions (Fig 2). In session 1, an AAD will be assigned to every participant and taken for at least 3 months. If patients have persistent AF, cardioversion will be performed with AAD. During the follow-up, those with recurrent AF should step up to session 2, which involves treatment with radiofrequency ablation (RFA) or CRYO-balloon ablation (4 pulmonary vein isolation; 4PVI). For participants of session 2, the follow-up will begin with the moment RFA or cryotherapy is applied, which will be regarded as 0-month; follow-up will be conducted every 3 months for the next 12 months. The rhythm control strategy will be conducted as per the clinical guidelines of 2020 ESC [30] and 2019 AHA/ACC/HRS guidelines [20] for AF.

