During patient monitoring, if AF recurs and the patient complains of its symptoms, RFA or cryoablation (4PVI) will be performed at the discretion of the physician in accordance with the 2020 ESC [30] 2019 AHA/ACC/HRS guidelines [20] for AF. For patients with ablation, 24-h Holter ECG monitoring every 3 months for an additional year will be performed from that point on. If severe adverse events occur, the patient will be excluded from the study after a committee meeting. The main concern of the review is the recurrence of AF, which is the primary outcome of this trial.

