Several systemic reviews and meta-analyses have described advantages of catheter ablation over AAD in maintaining sinus rhythm [38–42] and improving the quality of life [43]. The CABANA trial showed that catheter ablation was superior in reducing the recurrence rate of AF compared to the AAD-only therapy [44]. Assuming that catheter ablation will improve the clinical outcome and lower the AF recurrence rate compared to that achieved with the AAD-only treatment in patients with AF and DM, we will add the following procedures after the random assignment of SGLT-2 inhibitors to minimize the bias caused by study protocols: First, the patient takes the assigned medicine for at least 3 months. Second, if AF recurrence is detected and the patient manifests clinical symptoms at follow-up visits, the physician will make a clinical decision on catheter ablation. AF recurrence after ablation (RFA and 4PVI) within a year will be measured by using the established protocol as the primary outcome among patients who have underwent ablation. In this setting, however, comparing the AF burden between the case (SGLT-2 inhibitor) and control (non-SGLT-2 inhibitor) groups at 12 months of trial would disturb the study results. Thus, the recurrence of AF is set as the primary outcome in each step (AAD and ablation).

Previous studies, including DAPA-HF, EMPORER-Reduced, and DECLARE-TIMI 58, have focused on the efficacy of SGLT-2 inhibitors in reducing the risk of adverse cardiovascular events as the primary endpoint in patients with DM, HF, or AF. However, the effects of SGLT-2 inhibitors on arrhythmia, especially AF, were only described by subgroup post-hoc analyses or meta-analyses, so they usually focused on the AF incidence rate and could not analyze other specific properties of AF [16,32,45]. Thus, our trial was advantageous because it allowed the measurement of AF control prospectively in patients with AF and DM.

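### The 12-month and pre-ablation AF-burden comparisons are made within subsets defined by step-up, so randomisation does not protect them and a benefit from prevented recurrence is diluted or hidden

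*Protocol article*

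**What the plan says.** The Abstract names "change in AF burden, size of the left atrium, NT-proBNP" among the secondary outcomes. The Secondary outcomes section defines the measure: "AF burden is defined as the atrial fibrillation time percentage documented on 24-h Holter ECG".

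The comparison sets are given twice, in the text and in Table 1:

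- Without ablation, the text names the 3-month visit and then the "12-month follow-up visit in those who did not step up and used AAD only for rhythm control". Table 1 puts both visits in one item: "3-month F/U visit, 12-month F/U visit in those who did not step up to session 2".
- With ablation, Table 1 lists: "Immediately before trying ablation, 12-month F/U visit in those who stepped up to session 2".

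Entry to the second set is described in two ways. Study design and participants says "those with recurrent AF should step up to session 2", and the Study hypothesis section likewise ties step-up to recurrence. Follow-up and detection of AF recurrence says "if AF recurs and the patient complains of its symptoms, RFA or cryoablation (4PVI) will be performed at the discretion of the physician", and the Discussion also requires symptoms and a physician's decision.

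The Discussion recognises that ablation complicates a whole-arm comparison: comparing burden between the "groups at 12 months of trial would disturb the study results". It uses this to justify recurrence in each step as the primary outcome.

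**The concern.** Step-up happens after randomisation and depends on AF recurrence, the outcome that treatment is assumed to reduce (Statistical plan: 40%). A between-arm comparison restricted to patients who did, or did not, step up is therefore no longer a comparison of randomised groups. If SGLT-2 inhibitors prevent recurrence, patients who would have entered the ablation subset remain in the other one. The patients left in each subset then differ between arms, and the gain made by moving between subsets is not fully visible in either.

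AF burden matters to this trial although it is secondary. The Introduction and Discussion present quantified burden as something earlier studies rarely offer. A result close to no difference within the subsets could be reported as no effect on burden when the arms as randomised do differ.

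**Working it through.** The article gives no expected value, effect size or power for AF burden, so there is no figure of its own to reproduce. What follows is an illustration.

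**Inputs**

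- From the Statistical plan: a 40% reduction in AF and a 50% step-up share among AAD users. The control recurrence rate is not stated.
- Assumed: recurrence p of 50% in control and 50% × 0.6 = 30% with SGLT-2 inhibitors.
- Assumed: zero burden without recurrence. With recurrence and no ablation, mean burden b is 20% of time in both arms (case A), or 20% versus 12% (case B, where treatment also lowers burden among recurrences).
- Varied: s, the share of recurrences that step up, taken as equal in both arms.

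**Formulas**

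- Whole-arm mean, before any effect of ablation itself: p × b.
- No-step-up mean: p(1 − s)b / (1 − ps).

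**Whole arm**

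- Case A: 0.50 × 20 = 10.0 versus 0.30 × 20 = 6.0, a difference of 4.0 points.
- Case B: 10.0 versus 0.30 × 12 = 3.6, a difference of 6.4 points.

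**No-step-up subset.** Worked example, case A with s = 0.9: control 0.50 × 0.1 × 20 / (1 − 0.45) = 1.8; SGLT-2 0.30 × 0.1 × 20 / (1 − 0.27) = 0.8.

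| s | Case A: control vs SGLT-2 | Difference | Case B: control vs SGLT-2 | Difference |
|---|---|---|---|---|
| 100% | 0 vs 0 | 0 | 0 vs 0 | 0 |
| 90% | 1.8 vs 0.8 | 1.0 | 1.8 vs 0.5 | 1.3 |
| 75% | 4.0 vs 1.9 | 2.1 | 4.0 vs 1.2 | 2.8 |
| 50% | 6.7 vs 3.5 | 3.1 | 6.7 vs 2.1 | 4.5 |
| 25% | 8.6 vs 4.9 | 3.7 | 8.6 vs 2.9 | 5.7 |

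At s = 90% the subset keeps about a quarter of the whole-arm difference in case A (1.0/4.0) and a fifth in case B (1.3/6.4). With lower recurrence, 35% versus 21% (the same 40% reduction) and 20% burden in both arms, the whole-arm difference is 7.0 − 4.2 = 2.8. The subset difference at s = 90%, 75% and 50% is 0.5, 1.1 and 1.9.

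**AF first found at 12 months.** Suppose every earlier recurrence steps up. With a constant recurrence risk over four visits, the risk per visit is 1 − 0.50^(1/4) = 15.9% versus 1 − 0.70^(1/4) = 8.5%. Patients not yet stepped up at 12 months then have mean burden 0.159 × 20 = 3.2 versus 0.085 × 20 = 1.7 (case A) or 0.085 × 12 = 1.0 (case B). The subset difference is therefore not exactly zero even under the strict rule.

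**Pre-ablation comparison.** It is 20 versus 20 in case A at every s, so prevented recurrences leave no trace there. In case B it is 20 versus 12. These values follow from the assumption about b. Recurrence requires only AF lasting more than 30 s, which is 30/86,400 = 0.035% of a 24-hour recording, so the pre-ablation level could in practice be low or high.

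**Timing.** Study design and participants restarts the clock at ablation. If the stepped-up patients' 12-month visit follows that clock, it falls at least about 3 + 12 = 15 months after treatment starts, against 12 months for the others. The two subset results then cannot simply be combined into a 12-month comparison by arm.

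**The case against.** **The subset comparison might be thought empty.** A reader might infer that the no-step-up burden must be near zero in both arms, so that no real effect could appear. The documents do not support that. It needs every recurrence to step up and none to be first found at 12 months. Under the rule in the Follow-up section and the Discussion, patients with asymptomatic or non-ablated recurrence stay in the no-step-up set and carry burden. The effect is diluted and subject to selection, but not erased. A uniformly high pre-ablation burden is likewise an assumption, not something the protocol imposes.

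**The 3-month comparison may already be whole-arm.** In the text of Secondary outcomes the no-step-up qualifier attaches naturally to the 12-month visit, and at least 3 months of AAD come first. This is a fair reading and largely stands. Table 1, however, places the 3-month visit inside the no-step-up item, so the scope should be stated.

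**Prevented recurrence is captured elsewhere.** The primary outcome, AF-free survival, ablation rate and stable sinus rhythm do not rest on this split, and sinus rhythm is expressly compared in all participants whether or not ablated. This limits the consequence: the primary test is untouched. It does not rescue the 12-month burden comparisons, and it shows that an as-randomised comparison is compatible with the design.

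**A whole-arm 12-month comparison is disturbed by ablation.** This is true, and the Discussion says so. It calls for an explicit handling of ablation; conditioning on step-up exchanges that disturbance for selection.

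**Baseline adjustment and use of the 6- and 9-month Holters** can be left to an analysis plan that is not shown. Their absence is not counted here; they appear only as part of the remedy.

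**Conclusion.** The point holds for the 12-month and pre-ablation AF-burden comparisons. Both are fixed in the article within subsets defined by a post-randomisation event that treatment is expected to change, and no 12-month comparison by randomised arm is listed. A benefit that works by preventing recurrence is diluted. In the illustration, a whole-arm difference of 4.0 to 6.4 points falls to 3.1–4.5 points if half of recurrences step up and to 1.0–1.3 points if 90% do. It is zero only in the limiting case described above.

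These sizes rest on assumed recurrence and burden values, on equal step-up shares in both arms, and on ignoring ablation's own effect in the whole-arm figures. The direction of the dilution follows from the design, but its size cannot be fixed while the article gives two step-up rules. It would go too far to conclude that the burden objective cannot be answered, because the 3-month comparison can answer it once its scope is stated. The matter should be corrected, but it concerns a secondary outcome.

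**What to change.** 1. State that the main AF-burden comparison is the 3-month Holter in all randomised patients, adjusted for baseline Holter burden. Remove the ambiguity in Table 1.
2. As support, add a burden comparison by randomised arm over the follow-up Holters, timed from randomisation. State how ablation is handled as an intercurrent event, and how visits on the clock restarted at ablation are mapped to time since randomisation. An average taken regardless of ablation includes ablation's effect, so the text should say whether that is the intended question.
3. Label the step-up and no-step-up comparisons as descriptive and non-randomised.
4. Reconcile the step-up rule in Study hypothesis and Study design with the one in Follow-up and the Discussion, since it determines who is in each subset.

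The cost is mainly wording. The baseline and 3-month Holters are already scheduled for everyone in Table 5. The main burden result would reflect 3 rather than 12 months of treatment, which is a small loss. The supportive analysis needs some care, because Holters in ablated patients may not fall at 6, 9 and 12 months from randomisation.
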